#### Elimination criteria

Self-withdrawal or loss of visits by subjects;Those who have not reached 2 treatments; andThose who experience serious adverse reactions or adverse events during treatment.

(Note: Subjects who are dislodged should be accounted for, and their study medical records should be retained for review and not included in the final statistical analyses.)

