## Introduction

Postherpetic neuralgia (PHN) refers to a type of pain that persists for a duration of 1 month or longer, following the healing of an acute herpes zoster (HZ) rash (1). Epidemiological studies have shown that the occurrence rate of HZ in Europe, North America and the Asia Pacific region stands at 5 to 6 cases per 1,000 individuals per year and up to 30% of HZ patients develop PHN (2, 3). In China, the rate of PHN incidence is rising steadily each year, and the incidence increases with age (4). Clinical studies have found that PHN occurs mostly in the elderly, where the occurrence rate of PHN among patients aged over 50 can reach as high as 60 to 75%, which has a significant impact on both physical and mental well-being, as well as the overall quality of life (5, 6).

PHN, as a pain disorder that severely affects the quality of human life, faces many clinical challenges. One of the most problematic issues is the treatment of cephalo-facial PHN in patients aged 50 and above. The clinical challenges of cephalo-facial PHN in patients over 50 years of age are more daunting (7, 8), making the clinical symptoms of cephalo-facial PHN in patients over 50 years of age more complex and more difficult to treat. Therefore, this project will focus on patients over the age of 50 with cephalo-facial PHN for research.

Currently, the main clinical treatment options for PHN include drug therapy (9–11) and surgical treatment (12, 13) and alternative medicine (14, 15). Pregabalin has proven efficacy in the treatment of PHN (16) and is classified as a first-line clinical medication by guidelines (17); therefore, this study will use pregabalin as a control to investigate the clinical efficacy and safety of EA in patients with PHN. However, all of these treatment options have limitations. Studies have shown that 81.82% of patients with PHN still suffer from a similar degree of pain as before treatment, and their probability of adverse drug reactions is as high as 42.74% (18, 19). Although surgical treatment is effective for PHN, there is a greater risk of irreversible damage to the nerves and complications for patients over 50 years of age with cephalo-facial PHN (20). Therefore, there is an urgent need for alternative approaches to explore simpler, more convenient, effective, and inexpensive treatment options in the clinical treatment of cephalo-facial PHN over 50 years of age.

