#### Discontinuation criteria

A physician responsible for diagnosis assesses exacerbations of PHN occurring during the study, and when a patient experiences facial pain symptoms that persisted despite acupuncture treatment, as indicated by a VAS score exceeding 8, the physician evaluates the severity and subsequently discontinues the study;The specialist assesses the occurrence of significant adverse reactions during the study to make a decision on whether to proceed or discontinue the research;Participants who encounter severe complications or illnesses during the study that necessitate urgent medical attention; andParticipants who have additional reasons that prevent them from continuing with this study.

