### Sample size estimation

This research involves a randomized controlled trial design, where eligible participants will be allocated to two distinct groups in an equal proportion of one participant to another (1:1 ratio), and the primary outcome metric is the percentage of cases with a pain intensity VAS ≤ 2 points after 4 weeks of treatment. According to the project team’s pre-efficacy observation pre-trial, the effective rate of this study’s treatment regimen in treating PHN is about 91%, and the literature reported that the effective rate of pregabalin is 74.4% (49). The estimation of the required sample size formula for the test of superiority of the independent sample rate of two groups is used for the calculation, taking *α* = 0.025 and *β* = 0.2, with the same number of sample cases between the groups, and using a one-sided test, taking into account a 20% dropout rate. Each group will necessitate a minimum of 62 cases, resulting in a combined total of 124 cases across the two groups.

$$N=\frac{2{\left[Z_{\alpha /2}\sqrt{2\bar{p}\bar{q}}+Z_{\beta }\sqrt{p_{0}q_{0}+p_{1}q_{1}}\right]}^{2}}{{\left(p0-p1\right)}^{2}}$$

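### The elimination rule takes randomised patients out of the final analyses because of events after allocation, and makes no exception for safety

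*Protocol article*

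**What the plan says.** The Elimination criteria section of the protocol article names three groups. The first is "Self-withdrawal or loss of visits by subjects". The other two are "Those who have not reached 2 treatments; andThose who experience serious adverse reactions or adverse events during treatment". The note beneath the list says that these subjects must be accounted for, but that "their study medical records should be retained for review and not included in the final statistical analyses". It draws no line between efficacy and safety analyses.

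Three other sections bear on this:

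- Sample size estimation plans 62 patients per arm, "taking into account a 20% dropout rate".
- Quality control and data management has withdrawal reasons recorded and the dropout rate analysed. It does not bring the outcome data of these patients back into the analysis.
- Statistical analysis names the tests and a two-sided 5% level, but no analysis population.

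The Conclusion makes both effectiveness and safety against medication objectives of the trial. Safety evaluation has adverse events recorded throughout treatment and follow-up.

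**The concern.** Randomisation makes the arms comparable at allocation. A rule that then removes patients for what happens to them under treatment can undo that balance. Each of the three criteria can be related to the assigned arm, to the outcome, or to both.

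- **Withdrawal or loss.** The electroacupuncture (EA) arm attends three sessions a week of over an hour each, which the Limitations section itself calls less convenient than taking medication at home. Reasons for leaving may therefore differ between arms.
- **Fewer than 2 treatments.** This has a clear meaning for 12 EA sessions. The article does not say what a treatment is for capsules taken twice a day, so the criterion cannot be applied alike in both arms.
- **Adverse events.** The events that a safety comparison most needs are themselves the ground for removing the patient.

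At stake are the validity of the primary comparison, the level of the response rates to be reported, and the safety objective.

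**Working it through.** **Inputs from the documents.** From Sample size estimation: pregabalin response 74.4%, EA response 91%, 62 per arm, 20% dropout, "taking *α* = 0.025 and *β* = 0.2", one-sided. From Statistical analysis: two-sided tests at 0.05. The response measure is the one used for sizing, VAS of 2 or less after 4 weeks.

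**The plan's own figure.** The stated rates, one-sided alpha 0.025 and 80% power give 81 per arm before dropout (pooled-variance formula), and 81 / 0.8, rounded up, gives 102 after it. The stated 62 is not reproduced. That is a separate matter; here 62 is taken as planned. Removing 20% leaves 62 × 0.8 = 49.6, about 50 per arm.

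**Assumptions of the illustration.** True response is 74.4% in both arms, so there is no treatment effect. Each arm loses 20%. Let f be the share of an arm's losses who are non-responders. The documents give no value for f, so a range is shown. The rate among those analysed is

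analysed rate = (0.744 − 0.2 × (1 − f)) / 0.8

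- f = 0.256 (loss unrelated to response): (0.744 − 0.1488) / 0.8 = 74.4%
- f = 0.6: (0.744 − 0.08) / 0.8 = 83.0%
- f = 0.8: (0.744 − 0.04) / 0.8 = 88.0%

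**Chance of a false finding.** This is the exact binomial probability that a Pearson test at two-sided 0.05, with 50 per arm, declares arm A better when there is no true difference:

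| f in arm A | f in arm B | analysed rates (A, B) | A falsely favoured |
|---|---|---|---|
| 0.256 | 0.256 | 74.4%, 74.4% | 2.5% |
| 0.6 | 0.256 | 83%, 74.4% | 18.3% |
| 0.8 | 0.256 | 88%, 74.4% | 42.7% |
| 0.8 | 0.6 | 88%, 83% | 11% |
| 0.6 | 0.6 | 83%, 83% | 2.7% |
| 0.8 | 0.8 | 88%, 88% | 2.7% |

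Arm A may be EA or pregabalin; the table is the same either way. With 10% loss in each arm (about 56 analysed) and informative loss in arm A only, the 18% to 43% falls to about 7% to 12%.

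**Safety.** No arithmetic is needed. The Conclusion promises a comparison of safety with medication, and Safety evaluation collects the events. The elimination note then keeps patients with serious events out of the final statistical analyses. The three sections cannot all be followed.

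**The case against.** The strongest defence concerns size and direction. The 18% to 43% requires informative loss in one arm and uninformative loss in the other, and no section supports that asymmetry. With equally informative loss the error rate is essentially nominal. This stands. A reader might infer that the rule favours EA, because patients without benefit have reason to leave the arm with the heavier visit burden. Removal for adverse drug reactions could equally make loss informative in the pregabalin arm, so the documents do not fix a direction.

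Three other stronger readings are tempting and are not supported.

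- **Large-scale removal from the pregabalin arm.** The Introduction says of treated patients that "their probability of adverse drug reactions is as high as 42.74" per cent. It gives this as an upper value after remarks on treatment options in general, not as the pregabalin rate. Applying it to this rule would also require reading the third criterion as covering events of any severity. The wording leaves that scope unclear and should be clarified, but it supports no count of patients.
- **An empty safety analysis.** Records are retained, patients are accounted for and events are collected, so they could be listed by arm. The defect is that the statistical comparison has no safety exception.
- **Deletion of EA failures through the stopping rule.** The first of the Discontinuation criteria concerns "facial pain symptoms that persisted despite acupuncture treatment, as indicated by a VAS score exceeding 8". Discontinuation is not itself an elimination criterion, so a path from that stop to removal is inference.

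It could also be said that analysis sets belong in a statistical analysis plan that is not shown. That does not help here: the article is not silent but fixes an exclusion, and a plan with an intention-to-treat or safety set would contradict it.

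**Conclusion.** The point holds on the text. As written, the final analyses leave out randomised patients for reasons that arise after allocation and may depend on treatment and outcome, and nothing else in the article overrides this. The efficacy comparison is then not the randomised one, and the statistical safety comparison lacks the patients with serious events.

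The size and direction of the bias are unknown. The range from about 2.7% to 43% for a one-directional false finding rests on an assumed common response of 74.4%, 20% loss in each arm, and assumed non-responder shares of 60% to 80% among informative losses. Even in the benign case of equal loss, the reported response rates would be about 9 to 14 percentage points too high (83% or 88% against 74.4%). Confidence is high in the defect of wording and low in any particular magnitude. It should be corrected before any analysis.

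**What to change.** Replace the note under Elimination criteria with wording to this effect:

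- All randomised patients are analysed for efficacy in their assigned arm.
- Patients who stop treatment keep their scheduled assessments.
- Missing week-4 VAS is handled by a principled method, for example multiple imputation or a mixed model, with a sensitivity analysis counting missing as non-response.
- Everyone who received any treatment is in the safety analysis, including those with serious events.
- The present set is kept only as a per-protocol sensitivity analysis. For that purpose, define a treatment in the drug arm and say whether the third criterion covers serious events only.

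Separately, the first of the Discontinuation criteria mentions acupuncture only. It must be reconciled with the two-arm design.

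**Cost.** Protocol and analysis wording, and follow-up contact at visits already in Table 1. The effect may be diluted by non-adherence, and power will be lower than a completer analysis suggests. If 91% and 74.4% are rates among analysed patients, and 20% per arm are counted as non-responders, the rates become 0.91 × 0.8 = 72.8% and 0.744 × 0.8 = 59.5%. Power with 62 per arm at one-sided 0.025 is then about 34%, against about 59% for 50 completers per arm at the planned rates. That is the severe end, since it treats every missing patient as a failure, but the sponsor should see it before choosing the primary missing-data method.

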### Randomization and allocation concealment

The envelope randomization method will be used for randomization. Upon meeting both the inclusion and exclusion criteria, subjects will be enrolled into the study. The randomization personnel or clinical researchers will randomize them based on the pre prepared patient grouping envelopes. The randomization protocol for this study will be generated by the Clinical Evaluation Center at the subject’s institution, and this person will be not involved in the statistical analysis of this project. The randomization scheme for this study and the individual parameters set in the process of generating that scheme are collectively referred to as the blind bottom, which is sealed and signed by the person generating the randomization scheme and kept by a dedicated subject matter manager not involved in this project. Participants in subgroups are not involved in the statistical analysis of data. The evaluation of the efficacy indicators will be collected and organized by a person who is unaware of the subgroups, with a triple separation of the researcher, the acupuncture operator, and the statistician.

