### Participant enrollment

Participants are being recruited mainly from the Third Affiliated Hospital of Zhejiang Chinese Medical University and Zhejiang Hospital. Subject recruitment is carried out through multiple channels, with researchers focusing on following up with specialty outpatient clinics and regular screening of hospitalized patients, and active communication with patients. In addition, measures such as paper media and WeChat are regularly taken to recruit for the whole society.

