### Blinding

Because this project is a needling treatment, the needling operator must be in direct contact with the patient, to whom blindness cannot be applied. However, blinding is implemented for all other personnel involved in the study (including patients, those who recorded and entered the observational indicators, and the data statisticians), who will be unaware of the specific grouping of patients. To guarantee a more effective execution of the blind approach, each patient will be treated individually as much as possible, minimizing the need for patients to discuss with each other about the acupuncture treatment method, their feelings during the acupuncture, and the effects of the treatment.

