The SDS is a self-assessment tool designed to evaluate depressive states in adults, comprising 20 items that address depression-related symptoms such as low mood, diminished interest, sleep disturbances, and appetite changes. Its primary function is to rapidly screen for the presence and severity of depressive symptoms, providing valuable reference for clinical diagnosis and psychological evaluation (25). During administration, respondents rate each item based on their actual experiences over the past week using a 4-point Likert scale (1–4 points). The raw scores of all items are summed to obtain a total score, which is then converted into a standardized score to determine the level of depression (below 53: normal; 53–62: mild depression; 63–72: moderate depression; above 72: severe depression).

The HAMD is a widely used clinician-administered tool for assessing the severity of depressive symptoms (46). It is evaluated by trained professionals through patient interviews and clinical observations. The scale encompasses over 20 symptom domains, including depressed mood, feelings of guilt, suicidal ideation, sleep disturbances, loss of interest in work, psychomotor retardation, agitation, anxiety, and others, with each item rated on a 5-point Likert scale (0–4). Higher total scores indicate greater severity of depressive symptoms, with typical classifications as follows: below 7 points suggesting no depression, 7–17 points indicating mild depression, 18–24 points representing moderate depression, and scores above 24 denoting severe depression.

The SF-36 is a widely utilized generic self-administered questionnaire for assessing health-related quality of life (HRQoL). It comprises 36 items covering eight dimensions: physical functioning, role-physical, bodily pain, general health perceptions, vitality, social functioning, role-emotional, and mental health. Its primary purpose is to comprehensively evaluate an individual’s physiological, psychological, and social functional status, and it has been extensively applied in evaluating HRQoL and intervention outcomes among patients with postherpetic neuralgia (47, 48). During administration, respondents answer based on their actual conditions over the past 4 weeks. Scores for each dimension are calculated using standardized scoring algorithms and transformed into a 0–100 scale, with higher scores indicating better health status in that specific dimension.

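### The randomisation and blinding sections contradict each other on who knows the allocation, and the text lets a recruiting researcher handle the envelopes

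*Protocol article*

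**What the plan says.** Three sections of the protocol article bear on this point.

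- **Randomization and allocation concealment.** Envelopes are used once a patient has met the criteria and been enrolled: "The randomization personnel or clinical researchers will randomize them based on the pre prepared patient grouping envelopes". The randomisation scheme and its parameters are sealed, signed and held by a manager outside the project. Efficacy data are to be collected by someone who does not know the groups, "with a triple separation of the researcher, the acupuncture operator, and the statistician".
- **Blinding.** One role is exempt: "the needling operator must be in direct contact with the patient, to whom blindness cannot be applied". For the rest, "blinding is implemented for all other personnel involved in the study". The section names patients, those who record and enter the observations, and the statisticians, and describes the blinded people as those "who will be unaware of the specific grouping of patients".
- **Participant enrollment.** Recruitment runs through several channels, with "researchers focusing on following up with specialty outpatient clinics and regular screening of hospitalized patients, and active communication with patients".

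**The concern.** There are two linked problems.

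The first is a plain inconsistency. The article gives some staff a task that reveals the allocation, and then says that nobody but the needling operator knows it. A reader, auditor or site cannot tell from this text who is meant to be blinded.

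The second is a risk that the stated roles leave open. If the person who approaches and screens patients also works the envelopes, that person knows the allocations already made and may have access to the next one. Foreknowledge of that kind acts before enrolment, through the choice of whom to approach, when, and how to judge eligibility. Some exclusion criteria call for judgement, such as how well hypertension or diabetes is controlled, or whether an illness prevents cooperation with treatment.

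This matters more here than in many trials. The arms are needling and capsules, the primary outcome is self-rated pain, and the Limitations section accepts that patients may see through the blind. Allocation concealment, unlike patient blinding, can be fully achieved in this design, so there is no reason to leave it exposed.

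**Working it through.** No arithmetic applies. The point turns on roles, so the check sets the sections side by side.

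1. **Who learns the group through randomising?** The randomisation section allows two kinds of staff to do it: randomisation personnel, or clinical researchers. Randomising from a grouping envelope means reading the assignment, so whoever does it knows the group.
2. **Who is allowed to know the group?** Under the Blinding section, only the needling operator. All other personnel are described as unaware.
3. **Could the clinical researcher be the needling operator and so fall under the exemption?** No. The randomisation section itself separates the researcher, the acupuncture operator and the statistician.
4. **Does the conflict disappear if only randomisation personnel open envelopes?** No. They are not the needling operator either, so the Blinding section is wrong about them as well. Removing the clinical researchers from the randomisation sentence does not cure the contradiction unless the Blinding section is also changed.
5. **Are recruiters kept away from the envelopes?** The article states these safeguards:
   - the person who generates the scheme takes no part in the statistical analysis;
   - the master scheme is sealed and kept outside the project;
   - researcher, operator and statistician are separate;
   - the efficacy data collector does not know the groups.

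   None of these separates the researchers who screen and recruit from the clinical researchers who may randomise. The sealing and outside custody are stated for the master scheme, not for the envelopes in use.
6. **Is outcome assessment affected?** The randomisation section, the Blinding section and the Limitations section all state that those who assess or record outcomes are blinded. Nothing in steps 1 to 5 contradicts that.

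Steps 1 to 4 establish a literal contradiction. Step 5 establishes that an overlap of roles is permitted. It does not establish that the overlap occurs.

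**The case against.** The strongest reply is that weakened concealment is inferred. Eligibility and enrolment come before randomisation. An investigator who opens an envelope after enrolment does no harm unless envelopes can be read, reordered or opened early. That depends on sealing, opacity, numbering and custody, which an article may leave to the full protocol. The article does not say who holds the envelopes, nor that the researchers who recruit are the same people as the clinical researchers who may randomise. This stands to the extent that the concealment point is a risk and not a breach. It does not remove the point, because what is challenged is a permission in the text and not a missing detail. More detail on the envelopes would leave the two sections in conflict.

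Two stronger readings are tempting, and the document supports neither.

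- **Biased outcome rating.** A reader might infer that the researcher who randomises could sway the clinician-rated HAMD or the patients' VAS scores. For the HAMD the article says only "It is evaluated by trained professionals through patient interviews and clinical observations". It does not link those raters to the staff who randomise, and it states separately that efficacy data are collected by someone unaware of the groups.
- **A calculable rate of guessing the next allocation.** A reader might want to express the risk as the chance of predicting the next assignment. Such a figure needs a blocked scheme and a known block size. The article mentions no blocks and says that the scheme's parameters are sealed. The figure would also measure knowledge of past allocations. Site staff could gain that knowledge from the visibly different treatments, whoever opens the envelopes.

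**Conclusion.** The contradiction holds as written: the randomisation section and the Blinding section cannot both be true, for the clinical researchers and for the randomisation personnel alike. The consequence for allocation concealment is a permitted, avoidable risk. Its size is unknown and should not be given a number. This part rests on one reading, that nothing in the article keeps the recruiting researchers from also being the clinical researchers who randomise. If the full protocol separates them, the concealment risk falls away, but the Blinding section would still need correcting. The stated blinding of outcome assessment is not called into question. The point is worth correcting because selection bias arises before any outcome is measured, so a blinded assessor cannot repair it.

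**What to change.** Make both changes; the first alone leaves the contradiction in place.

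1. **Randomization and allocation concealment.** Remove the option for clinical researchers to randomise. State that only the randomisation personnel, who do not recruit, screen or rate outcomes, open the next envelope. State that they do so only after eligibility and baseline scores are recorded, and that they pass the result only to those delivering treatment.
2. **Blinding.** List the randomisation personnel as unblinded alongside the needling operator, and limit the claim of blinding to the roles that really are blinded. Anyone else who is told the result in order to deliver treatment belongs on the unblinded list too.

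The cost is a change of wording and of task delegation, with no change to patients, visits or design. The randomisation personnel are already named in the plan, but the article does not say that they are present at each hospital or that they have no recruiting role, so the sponsor must confirm both. The small downside is that they must be reachable at both centres whenever a patient enrols.
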